### Secondary Estimands

4.2

Secondary outcomes are defined per ICU care episode. ICU length of stay is the time from ICU admission to ICU discharge or death. The durations of invasive mechanical ventilation, noninvasive ventilation, and CRRT are the cumulative hours of each therapy during the ICU episode, as registered in SIR; because death precludes further accrual of these durations, they are analyzed in a time‐to‐event framework with death handled as a competing event. Unplanned ICU readmission is defined, per the SIR definition, as an unplanned return to intensive care within 72 h of ICU discharge, recorded as a binary outcome per discharged episode.

Testing‐intensity outcomes, referred to elsewhere in this protocol as process outcomes, are the number of ABG samples, venous laboratory tests, and chest radiographs per patient‐day.

The environmental outcome—climate impact expressed as carbon dioxide equivalents (CO_2_e, 100‐year global warming potential) attributable to blood gas sampling, laboratory testing, and chest radiography—will be estimated from the process‐outcome counts combined with published and supplier‐derived emission factors per test, with the functional unit being CO_2_e per patient‐day; a separate prespecified analysis plan will detail data sources, system boundaries, and methods, and this outcome is exploratory. Because death precludes the further accrual of tests and of their associated emissions, an intervention that increased early mortality would mechanically appear favorable on both testing intensity and CO_2_e. These outcomes are therefore subordinate to the primary safety outcome: they are interpreted as evidence of benefit only if non‐inferiority for 30‐day mortality is demonstrated, and if it is not, they are reported descriptively with no efficiency or environmental claim made. All such outcomes are expressed per patient‐day as well as per care episode, so that any shortening of the denominator through earlier death remains visible.

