#### Non‐Inferiority Power Analysis

4.4.1

We conducted a non‐inferiority‐based power calculation for our primary outcome of mortality, using a non‐inferiority margin of 3%. The analysis is based on data from the SIR.

The choice of a 3‐percentage‐point margin was made on the following grounds. First, the intervention removes routine, non‐indicated testing while explicitly preserving all clinically indicated diagnostics, and the aggregate randomized and observational evidence on diagnostic‐test reduction in intensive care shows no signal of increased mortality [22]; a true effect approaching the margin is therefore considered implausible a priori. Second, mortality is deliberately complemented by more sensitive safety outcomes that would be expected to deteriorate before any mortality effect became detectable, together with monthly safety monitoring throughout the trial. Third, the margin must be weighed against feasibility: demonstrating non‐inferiority within a substantially narrower margin (e.g., 1–2 percentage points) would require a trial several times larger, running over multiple years, which is not achievable while ICUs are already adopting CW practice outside trial conditions; the present design represents the strongest randomized evidence obtainable before uncontrolled implementation makes a controlled evaluation impossible. On balance, the steering committee judged that, for an intervention with documented benefits in reduced iatrogenic anemia, reduced resource use and reduced environmental impact, a 3‐percentage‐point margin represents the largest mortality difference that could be considered clinically acceptable, while the a priori expected difference is null. The margin may also be set against those adopted in recent critical care non‐inferiority trials with all‐cause mortality as the primary outcome. EVERDAC, comparing early with deferred arterial catheterization in shock, used a margin of 5 percentage points against a control‐group 28‐day mortality of 36.9% [34]. BALANCE, comparing 7 with 14 days of antibiotic therapy for bloodstream infection, used 4 percentage points against a control‐group 90‐day mortality of 16.1% [35]; three earlier trials in that field used 10 percentage points. In absolute terms, the present margin is smaller than both. In relative terms, 3 percentage points against a baseline 30‐day mortality of 18% corresponds to a risk ratio of 1.17, which lies between the corresponding figures for EVERDAC and BALANCE. The choice of margin does not by itself determine what would justify a change in practice; that question is addressed in the Discussion. Expressed in absolute terms, a true effect lying exactly at the margin would correspond to approximately 670 additional deaths across the projected 22,428 care episodes. The trial is therefore designed to exclude, rather than to detect, harm of this magnitude, and the secondary safety outcomes together with monthly monitoring are intended to identify smaller signals earlier.

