Because the estimand is an absolute risk difference, adjusted marginal risks under intervention and control are obtained from the fitted model by regression standardization (g‐computation): the model is used to predict each episode's outcome probability under both treatment conditions, and these predictions are averaged over the trial population. The adjusted risk difference is the difference between the two standardized risks, with a 95% CI obtained by cluster bootstrap or delta method. Non‐inferiority is declared if the upper bound of the two‐sided 95% CI (equivalently the one‐sided 97.5% bound) for the adjusted risk difference (intervention minus control) lies below 3 percentage points. Intention‐to‐treat analysis behaves differently in a non‐inferiority trial than in a superiority trial. Whereas incomplete adherence biases a superiority comparison toward the null and is therefore conservative, in a non‐inferiority comparison it makes the two conditions more alike and so makes a conclusion of non‐inferiority easier to reach; intention‐to‐treat is in this sense anti‐conservative [37]. We therefore prespecify a per‐protocol analysis alongside the primary intention‐to‐treat analysis. The per‐protocol population comprises all control periods together with those intervention cluster‐periods in which the cluster's own testing intensity met the fidelity criterion; cluster‐periods during which the intervention was paused or modified under the provisions above are excluded from the intervention condition. The per‐protocol analysis uses the same model, covariates, and non‐inferiority margin as the primary analysis. A conclusion of non‐inferiority requires the upper confidence bound to lie below the margin in both analyses. Where the two are discordant, both are reported, and the discordance is discussed rather than resolved by rule. Realized testing intensity is reported for both conditions at cluster level so that the separation achieved is visible to the reader.

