ICU length of stay and the durations of invasive ventilation, noninvasive ventilation, and CRRT are analyzed in a time‐to‐event framework, with time origin at ICU admission (for length of stay) or at initiation of the respective therapy (for therapy durations). The events of interest are, respectively, live ICU discharge and liberation from the therapy; death before the event is treated as a competing event using cause‐specific Cox proportional‐hazards models with a gamma‐distributed cluster‐level frailty to account for clustering, complemented by cause‐specific cumulative incidence functions. Episodes are administratively censored at 30 days from ICU admission for length of stay, and from initiation of the respective therapy for the durations of invasive ventilation, noninvasive ventilation, and CRRT; episodes still ongoing at that point are censored. Treating death as a competing event rather than censoring avoids the bias whereby early deaths masquerade as short, favorable stays. Proportional‐hazards assumptions are assessed with Schoenfeld residuals; where violated, effects are reported as time‐varying or summarized as restricted‐mean‐survival‐time differences. Models are adjusted for the same covariates as the primary analysis. Unplanned ICU readmission within 72 h is analyzed among live ICU discharges with a logistic generalized linear mixed‐effects model specified analogously to the primary analysis.

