### Safety Monitoring

5.8

A formal data monitoring committee with interim efficacy analyses is not established, which we consider justified by the pragmatic registry‐based design, the minimal‐risk nature of an intervention that removes only non‐indicated routine testing while preserving all clinically indicated diagnostics, and the absence of any planned early stopping for benefit. Safety oversight is instead provided by an independent safety review group comprising [name] and [name], both senior intensivists with deep knowledge of SIR data, none of whom are trial investigators.

The group reviews unblinded monthly reports generated from SIR, comprising 30‐day mortality and the secondary safety outcomes by cluster and by intervention status, until the last patient has completed follow‐up. The group may recommend continuation, modification, suspension of the intervention at individual ICUs, or termination of the trial; recommendations are made to the principal investigator and steering committee, who are responsible for acting on them and for informing participating ICUs and, where required, the Swedish Ethical Review Authority. If interim monitoring indicates increasing mortality or adverse changes in any secondary safety outcome, the affected ICU will be contacted to discuss appropriate action. A quantitative trigger is prespecified. Review by the safety review group is initiated whenever a cluster's observed 30‐day mortality during its intervention periods exceeds the upper bound of the 95% prediction interval derived from that cluster's own historical SIR mortality for the corresponding calendar months, or whenever the pooled intervention‐versus‐control mortality difference on the cumulative monthly report exceeds 3 percentage points. Meeting a trigger prompts review and, at the group's discretion, contact with the affected unit and a recommendation to the steering committee; it does not automatically suspend the trial.

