### Harms

5.9

The conceivable harms of reducing routine diagnostics are delayed recognition of clinical deterioration, of laboratory derangements such as electrolyte disturbance or occult bleeding, or of mechanical complications such as pneumothorax or catheter malposition that routine imaging might otherwise detect. Because the trial is embedded in routine care and modifies testing defaults rather than introducing a therapeutic agent, harms are monitored at two levels. At the population level, the monthly safety reports track 30‐day mortality and the secondary safety outcomes by cluster and intervention status; these outcomes are deliberately chosen as sensitive upstream indicators that would deteriorate before mortality.

At the patient level, clinicians and local investigators are instructed to report any serious adverse event suspected to be related to reduced testing, in particular missed or delayed diagnoses with clinical consequences, to the principal investigator without undue delay after becoming aware of it. Causality is assessed by the independent safety review group, which reviews the case documentation and classifies events as unrelated, possibly related, or probably related to the intervention. Confirmed or suspected intervention‐related serious harms and any safety signal in the monthly reports trigger review by the safety review group, which may recommend pausing the intervention at the affected ICU or across the trial; such events are reported to the steering committee, the affected ICU, and, where required under Swedish regulations, the Swedish Ethical Review Authority. All reported events and actions taken are summarized in the trial publication. Patients are covered by the ordinary Swedish patient‐injury insurance (patientförsäkringen, LÖF).

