### Protocol Amendments

6.2

Protocol amendments are proposed to and approved by the steering committee. Substantive amendments—those affecting eligibility, the intervention, the outcomes, the analysis plan, or patient safety—are submitted to the Swedish Ethical Review Authority for approval before implementation, recorded in an updated protocol version with the date, the change, and its reason, reflected in the ClinicalTrials.gov record, and communicated to all participating units and to the independent safety review group. Non‐substantive administrative changes are recorded in the trial master file. All amendments will be reported in the trial publication.

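### Ventilation, NIV and CRRT are analysed only from therapy start to liberation, with no stated comparison of start rates, so as safety indicators they can miss or misread extra starts

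*Protocol article*

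**What the plan says.** Section 4.2 (Secondary Estimands) takes the ICU care episode as the unit and says the three therapy durations "are the cumulative hours of each therapy during the ICU episode, as registered in SIR". The same sentence assigns them to a time-to-event analysis with death as a competing event.

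Section 5.2 gives the model. The time origin is ICU admission for length of stay, "or at initiation of the respective therapy (for therapy durations"). The event is liberation, death is the competing event, and follow-up is censored 30 days after initiation. The model is a cause-specific Cox model with cluster frailty.

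Two sections give these outcomes a safety role. Section 4.4.1, as the second ground for the 3-point mortality margin, refers to "more sensitive safety outcomes that would be expected to deteriorate before any mortality effect became detectable". Section 5.9 (Harms) says "these outcomes are deliberately chosen as sensitive upstream indicators that would deteriorate before mortality". It also names the feared mechanism: "The conceivable harms of reducing routine diagnostics are delayed recognition of clinical deterioration, of laboratory derangements such as electrolyte disturbance or occult bleeding".

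Section 5.1 makes every secondary outcome supportive, with no formal non-inferiority test. Section 2.2 words the objectives as effects on duration.

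**The concern.** An episode that never starts a therapy has no time zero and cannot enter its liberation model. Starting is not always a baseline feature. A patient whose deterioration or laboratory derangement is recognised late may need intubation, NIV or CRRT after admission, in a unit already under the intervention. The compared groups are then partly selected by something the intervention can change.

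The harm that section 5.9 describes could plausibly appear first as extra starts, and the liberation models do not count starts. Depending on how long the added courses last, they show nothing, a slightly favourable result, or a partial harm signal. Three of the five clinical secondary outcomes in section 4.2 are of this kind. Length of stay, readmission and serious adverse event reports would reflect extra starts only indirectly. No primary, secondary, process, sensitivity or subgroup analysis in the article compares how often a therapy is started.

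**Working it through.** The plan states no figure on this point, so there is none to reproduce. The calculation shows the direction, which follows from the model, and a range of sizes, which rests on assumptions.

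**Inputs from the plan.** 36 clusters, 13 periods, 22,428 episodes (22,428 / 468 ≈ 48 per cell); censoring at 30 days = 720 h; ICC 0.009, which is the mortality value, borrowed here.

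**Assumed.** 40% of episodes ventilated; exponential courses with mean 96 h; 20% dying on therapy; switches at months 2 to 11 (Figure 1 is not shown); two higher ICC settings for start rates.

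**1. Intervention share and extra starts.** With 36 clusters, six sequences hold four clusters and four hold three. Intervention months per sequence run from 12 down to 3.
- Larger sequences first: 4×(12+11+10+9+8+7) + 3×(6+5+4+3) = 282 of 468 cells = 60.3%, or 13,514 episodes.
- Larger sequences last: 3×(12+11+10+9) + 4×(8+7+6+5+4+3) = 258 of 468 = 55.1%, or 12,364 episodes.
- A rise from 40% to 44% (10% more starts) adds 0.04 × 12,364 = 495 to 0.04 × 13,514 = 541 starts.

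**2. Direction.** Let a = 1/96 be the exit rate of usual courses, b = a/r that of added courses (r = added/usual mean length), and e the relative increase in starts. Usual courses are left unchanged. The intervention/control ratio of liberation hazards at time t is

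[a·exp(−at) + e·b·exp(−bt)] / {a·[exp(−at) + e·exp(−bt)]}.

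If r = 1 this equals 1 at every t, for any e: extra starts of usual length are invisible. At t = 0 it is (1 + e/r)/(1 + e), above 1 for short added courses and below 1 for long ones.

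**3. Size.** Large-sample Cox hazard ratio for liberation, censored at 720 h:

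| Extra starts | r = 0.25 | 0.5 | 1 | 1.5 | 2 |
|---|---|---|---|---|---|
| 10% | 1.07 | 1.05 | 1.00 | 0.96 | 0.92 |
| 5% | 1.04 | 1.02 | 1.00 | 0.98 | 0.96 |
| 2.5% | 1.02 | 1.01 | 1.00 | 0.99 | 0.98 |

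The 10% row treats every start as modifiable. The 5% and 2.5% rows are a 10% rise in post-admission starts when these are half or a quarter of all starts.

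**4. What the model would report.** The variance of the treatment indicator after removing cluster and period effects is 0.0772. There are about 22,428 × 0.42 = 9,420 starters. SE(log HR) = 1/√(events × 0.077) = 0.042 if 80% are liberated and 0.037 if all are. For 10% extra starts, the chance that the 95% CI shows apparent benefit is 39-47% at r = 0.25. The chance that it shows harm is 18-22% at r = 1.5 and 50-59% at r = 2. For 5% and 2.5% extra starts, apparent benefit at r = 0.25 falls to about 14-16% and 7%.

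**5. What a start-rate comparison would show.** Generalised least squares with cluster and cluster-by-period effects; power = Φ(difference/SE − 1.96). CAC is the cluster autocorrelation.

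| Setting | SE (points) | Power, 4 points | 2 points | 1 point |
|---|---|---|---|---|
| ICC 0.009, CAC 1 | 1.13 | 94% | 43% | 14% |
| ICC 0.10, CAC 0.8 | 1.60 | 71% | 24% | 9% |

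An intermediate setting (ICC 0.05, CAC 0.8) gives SE 1.40 and 82% power for 4 points. The 95% CI half-width is 2.2 to 3.1 points. For rarer therapies, power for a 10% relative rise in all starts is 30-17% at a 10% base rate and 16-10% at 5%.

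**The case against.** The strongest reply is that nothing here is an error. The objectives concern duration, and time from initiation to liberation is a valid way to study duration among those treated. That stands, and the fix therefore leaves the models in place.

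A reader might infer that sections 4.2 and 5.2 contradict each other. They do not. Section 4.2 itself sends the durations to a time-to-event analysis, and taking the episode as unit does not promise that non-starters count as zero hours.

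A reader might also infer that the monthly safety reports share the gap. Section 5.8 says they cover mortality "and the secondary safety outcomes by cluster and by intervention status", without limiting them to starters, so that is not shown.

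The 10% case could be read as expected. It is a ceiling. Patients already on the therapy at admission are not selected by exposure, and the article gives no split. In the smaller cases the hazard ratio barely moves and the start-rate comparison has little power. Visible apparent benefit also needs added courses much shorter than usual, which delayed recognition does not obviously produce.

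The full protocol and analysis plan are deposited elsewhere (section 2.5), and a descriptive table of therapy use may well be there. The point does not rest on that silence: the article fixes origin, event and censoring for outcomes it presents as sensitive safety signals.

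Finally, a start rate is itself ambiguous, since fewer tests could delay or prevent starts. That is a fair limit and belongs in the interpretation.

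**Conclusion.** The point holds in a limited form. The liberation models answer the duration question but are incomplete as safety indicators, because extra starts of usual length leave the hazard ratio at exactly 1.00 and other extra starts move it in either direction. That much follows from the stated time origin. The size is unknown: the hazard ratios of 1.07 to 0.92, 1.04 to 0.96 and 1.02 to 0.98 depend on assumed start rates, course lengths and the share of starts after admission.

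It would go too far to say that the mortality conclusion or the 3-point margin is undermined. The primary analysis does not use these outcomes, they are supportive only, and they are one of several grounds given for the margin. This is a worthwhile, low-cost improvement to the secondary safety analysis.

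**What to change.** In sections 4.2 and 5.2:
- Add initiation of invasive ventilation, of NIV and of CRRT (yes/no, all care episodes) as supportive outcomes. Use the primary logistic mixed model and its standardised risk difference, for which the plan already says that "adjusted marginal risks under intervention and control are obtained from the fitted model by regression standardization".
- Label the three liberation models as conditional on initiation, to be read together with the start rates.
- State that a wide start-rate interval is not reassurance, and that a lower start rate may reflect delayed recognition as well as benefit.

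No change to section 5.8 is needed.

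**Cost.** Three supportive models on treatment data already listed for extraction (section 5.11.1.4), with no extra patients and no multiplicity consequence under section 5.1. Section 6.2 counts as substantive any changes that are "those affecting eligibility, the intervention, the outcomes, the analysis plan, or patient safety". This one therefore needs ethics approval before implementation, a new protocol version, a registry update, and notice to all units and the safety review group. It should be made before outcome data are extracted, the condition that section 2.5 reports for every version so far. Precision will be low for the rarer therapies.

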#### Cluster Definition

4.5.1

Individual ICUs represent clusters for randomization purposes, with one exception: where two ICUs have physicians and nurses working at both ICU sites in the same hospital. These two interconnected ICUs are seen as one cluster. SIR categorizes ICUs into Levels 1, 2, and 3 based on care level [36].

ICUs in Category 1 manage intensive care for patients with failure in all organ systems but lack most supporting resources. The hospital lacks access to most specialties and resources around the clock, for example, pediatrics, vascular surgery, ENT surgery, and blood bank. ICUs in Category 1 should be able to consult and send patients for care at ICUs in Categories 2 and 3. For this to work, ICUs in Category 1 must be able to receive patients with less complex needs from Category 2 and 3 units.

ICUs in Category 2 manage intensive care for patients with failure in all organ systems but lack Category 3's supporting resources. The hospital can still function as a referral center for the region, for example, for specialties such as pediatrics, vascular surgery, angiographic services, and/or ENT surgery. They therefore have access to most specialties, particularly emergency surgery, radiology, laboratory, and blood bank around the clock. ICUs in Category 2 should be able to consult and send patients for care at ICUs in Category 3. For this to work, units within Category 2 must be able to receive patients with less complex needs from Category 3 units.

Category 3 consists primarily of ICUs at university hospitals. These provide the most advanced monitoring and treatment methods for various types of organ failure. Since this category typically represents the full capacity of Swedish healthcare, they serve as referral centers for smaller hospitals. ICUs within Category 3 should have a system to oversee all the hospital's intensive care resources and have clear communication pathways into the hospital, preferably with a lead intensive care physician who can be reached on a dedicated phone line from referring hospitals. To function as a referral center with preparedness to receive the most complex patients regardless of place of residence, ICUs in Category 3 must also be able to transfer less complex intensive care patients to Category 1 and 2 units in the surrounding area.

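### A live transfer to another ICU falls by default into the length-of-stay event and has no defined outcome for the ventilation and CRRT durations

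*Protocol article*

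**What the plan says.** Section 4.2 sets the unit of analysis: "Secondary outcomes are defined per ICU care episode". It then defines the clocks. For length of stay, "ICU length of stay is the time from ICU admission to ICU discharge or death". The durations of invasive ventilation, noninvasive ventilation and CRRT "are the cumulative hours of each therapy during the ICU episode, as registered in SIR".

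Section 5.2 supplies the model, a cause-specific Cox model with cluster frailty. On events: "The events of interest are, respectively, live ICU discharge and liberation from the therapy". On competing risks: "death before the event is treated as a competing event". On censoring: "Episodes are administratively censored at 30 days from ICU admission for length of stay", with the same 30-day limit from start of therapy for the therapy durations. Unplanned readmission within 72 h is analysed among live ICU discharges and follows the registry's (SIR's) own definition, which the article does not reproduce.

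Neither section mentions transfer from one ICU to another. Section 4.5.1, describing the SIR care categories, says that Category 1 units "should be able to consult and send patients for care at ICUs in Categories 2 and 3". It says the same of Category 2 units towards Category 3, and it describes transfer of less complex patients back down.

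Section 5.9 calls the secondary safety outcomes "sensitive upstream indicators that would deteriorate before mortality". Section 4.4.1 uses them as one of its grounds for the 3-percentage-point margin.

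**The concern.** Section 5.2 makes death a competing event so that early deaths do not look like good, short stays. An upward transfer after deterioration can create the same appearance, and nothing guards against it.

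The first harm named in section 5.9 is late recognition of deterioration. In a Category 1 or 2 unit, one plausible consequence is that the patient is moved to a higher-category ICU. If that move ends the episode as a live discharge, the length-of-stay model records a quick discharge where intensive care has in fact continued, perhaps at greater intensity. An outcome that can improve when harm occurs is a weak early warning, and these outcomes also feed the monthly safety reports in section 5.8.

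The continued stay is not carried forward within the first episode. If the receiving unit takes part, the stay becomes a new episode, analysed under the condition prevailing there (section 4.1 states that rule for the primary estimand). If it does not, the stay drops out of these outcomes. Participating units cover about 53% of adult ICU admissions (section 3.4).

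**Working it through.** The plan states no transfer rate and no expected effect on these outcomes, so there is no figure to reproduce. The check compares the definitions and then illustrates direction on assumed inputs.

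**1. Length of stay.** Take a patient moved alive to another ICU on day 2 and test each exit in section 5.2:

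- death: no, the patient is alive;
- censoring at 30 days: no, it is day 2;
- live ICU discharge: the only exit left, since the unit is the single ICU episode and no discharge destination is named.

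The transfer is therefore counted as the event of interest. This follows from the closed list; the article does not state it outright.

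**2. Therapy durations.** Take the same patient, still ventilated or on CRRT. The patient has not been liberated, has not died and is not at 30 days. Hours stop being counted at the end of the episode, but no status is assigned. There are two obvious codings:

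- as liberation: an ongoing therapy is recorded as a success;
- as ordinary censoring: patients unlikely to be liberated soon leave the risk set, which raises the apparent liberation hazard among those who remain.

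Both tend to favour the condition with more such transfers.

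**3. Readmission.** A direct transfer could be left out, enter only the denominator, or count as an unplanned return. That depends on the SIR definition, which is not shown, so no direction can be given.

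**4. Direction and size for length of stay (assumed inputs).** Assume constant hazards. Let *s* be the share of live ICU discharges under control that are upward transfers, *d* the relative increase in the transfer hazard under intervention, and *h* the true hazard ratio for ordinary discharge. The hazard ratio for all live discharges is

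HR = (1 − s) × h + s × (1 + d)

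| s | d | HR if h = 1.00 | HR if h = 0.95 |
|---|---|---|---|
| 2% | 25% | 0.98 + 0.025 = 1.005 | 0.931 + 0.025 = 0.956 |
| 2% | 100% | 0.98 + 0.04 = 1.020 | 0.931 + 0.04 = 0.971 |
| 5% | 50% | 0.95 + 0.075 = 1.025 | 0.9025 + 0.075 = 0.978 |
| 5% | 100% | 0.95 + 0.10 = 1.050 | 0.9025 + 0.10 = 1.0025 |
| 10% | 25% | 0.90 + 0.125 = 1.025 | 0.855 + 0.125 = 0.980 |
| 10% | 50% | 0.90 + 0.15 = 1.050 | 0.855 + 0.15 = 1.005 |
| 10% | 100% | 0.90 + 0.20 = 1.100 | 0.855 + 0.20 = 1.055 |

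A hazard ratio above 1 reads as a shorter stay. With no true change in ordinary discharge, the estimate moves to between 1.005 and 1.10. With ordinary discharge truly 5% slower, it lies between 0.956 and 1.055 and passes 1 only at the upper end of the assumed range. With d = 0 and h = 0.95, HR = 0.95 + 0.05 × s, that is 0.951 at s = 2% and 0.955 at s = 10%: slight dilution and no reversal.

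**The case against.** The strongest reply is that the article never says a transfer is a discharge. It is silent, and section 2.5 says that fuller versions of the protocol and analysis plan are deposited elsewhere, where episode boundaries may be settled. Section 4.5.1 describes what each category of unit should be able to do and gives no transfer frequency. Section 5.1 makes the secondary outcomes supportive, without formal testing. Section 5.9 separately requires reporting of serious events suspected to result from reduced testing.

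Most of this stands as a limit on weight. It does not remove the length-of-stay point. There the article gives a complete list of exits, and applying that list as written classifies the transfer wrongly. That is a rule with a wrong consequence, and more than omitted detail.

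A reader might infer three stronger things that the documents do not support:

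- *That a patient transferred on a ventilator or CRRT is scored as a success.* The event is liberation, and on the plain wording that patient is not liberated. The episode is unassigned.
- *That the readmission outcome is distorted in the favourable direction.* This depends on the unseen SIR definition. If an unplanned upward transfer counted as a return, it would register as an adverse outcome.
- *That the treatment effect is biased.* That requires the frequency or type of transfer to differ by condition, and nothing in the documents shows that it will.

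**Conclusion.** The point holds for length of stay as a misclassification built into the stated definitions, and for the three therapy durations as an undefined outcome. It weakens the role that sections 4.4.1 and 5.9 give these measures as early signals of harm.

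The size is unknown. The hazard ratios shown rest on an assumed share of 2–10%, an assumed increase of 25–100% and constant hazards, and they show direction only. If transfers do not differ by condition, the consequence is mainly dilution. The confirmatory result is not affected by this event definition: 30-day mortality comes from the population register and captures deaths after transfer.

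**What to change.** In sections 4.2 and 5.2:

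1. Define the length-of-stay event as live discharge to a non-ICU destination.
2. Make ICU-to-ICU transfer a separate competing exit for length of stay, and for the therapy durations when therapy is ongoing at transfer.
3. Report the share of episodes ending in transfer by condition, with its cumulative incidence. This part is essential. In a cause-specific Cox model a competing exit leaves the risk set just as a censored episode does, so the hazard ratio for discharge or liberation cannot be read without the transfer results beside it.
4. Add a sensitivity analysis that joins contiguous episodes where they can be linked, assigned to the cluster and condition of first admission. Joining is better kept out of the main analysis: a joined stay spans two clusters and possibly two conditions, and linkage to nonparticipating units is not confirmed.
5. State whether direct transfers enter the 72-h readmission denominator.

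The cost is definition wording and some programming. SIR supplies discharge status (section 4.3), and route of admission with admission and discharge times (section 5.11.1.2). The primary model already needs a patient identifier. Results will no longer match SIR's per-episode figures. Because the change affects outcomes and analysis, it would follow the amendment route in section 6.2. It can still count as prespecified if, as section 2.5 reports for the versions so far, no outcome data have been extracted or examined.
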